## Methods

### Study design

This study is a multicentre randomised controlled clinical trial study conducted in four clinical centres (Figure 1). The Wuxi Hospital of Traditional Chinese Medicine is the main centre. The Yueyang Hospital of Integrative Medicine affiliated with the Shanghai University of Traditional Chinese Medicine, Wuxi Rehabilitation Hospital and the Wuxi Xinwu District Hospital of Traditional Chinese Medicine are the three subcentres. Patients were recruited through advertisements at each centre. Patients who met the inclusion criteria were randomly assigned to either the TCE group or the Tuina combined with TCE group at a 1:1 ratio. The trial consisted of a four-week intervention period and subsequent three- and six-month follow-up periods. Data were collected before treatment, after 4 weeks of treatment, and at 3 months and 6 months of follow-up. The outcome assessment indicators included the Oswestry Disability Index (ODI), Short Form of Quality of Life (SF-36) Scale, Short-Form McGill Pain Questionnaire (SF-MPQ) Scale and gait analysis, which was used only for efficacy evaluations before and after 4 weeks of treatment.

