### Sample size calculation

The trial was designed as a superiority trial with ODI as the primary observation index. The previous study demonstrated that the mean and standard deviation of ODI after 4 weeks of intervention in the TCEs group were 19.73 and 1.94, respectively, whereas the mean and standard deviation of ODI after 4 weeks of intervention in the Tuina combined with TCE group were 14.53 and 2.60, respectively. The sample size was calculated using the following formula:

$$n=\frac{2{\left(Z_{\alpha /2}+Z_{\beta }\right)}^{2}\times \sigma^{2}}{\left(\mu_{t}-\mu_{c}-\Delta \right)}$$

$$\mu_{t}=14.53,\mu_{c}=19.73,\alpha =0.05,\beta =0.2,\sigma =2.60,\Delta =-4$$

The sample size for each group was 74. Because this trial was a superiority trial, the sample size of each group was the same, and the clinical trial was set up in two groups (Tuina with TCE group and TCE group), combined with the relevant regulations. To evaluate the efficacy and safety of this study fully, the total number of cases was planned to be 166 cases, considering the potential for adverse effects. The Wuxi Hospital of Traditional Chinese Medicine was responsible for this project and was the main centre where the case study was undertaken. In other subcentres, the number of cases can be adjusted according to the situation, but no fewer than 30 cases should be in each group in each centre. If enrolment cannot be completed in any centre due to insufficient suitable subjects, the cases were distributed among the centres.

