### Adverse events

The treatment responses of all patients with lumbar intervertebral disc herniation who received Tuina in conjunction with TCEs were monitored and documented throughout the course of the study. Adverse events during the treatment period were recorded and analysed to ascertain whether it was related to the treatment. Adverse events included those that occurred during the clinical trial and resulted in hospitalisation, prolonged hospitalisation, disability, impairment of the ability to work, life-threatening injury or death. In case of any serious adverse event, whether related to the intervention, the trial should be terminated immediately and appropriate rescue treatment initiated without delay. Such incidents must also be reported within 24 h to the responsible unit, the ethics committee, the sponsoring organisation and the relevant personnel of the drug regulatory authority. The relevant information must be recorded in the case file.

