### Quality control

Prior to the implementation of the trial, ensuring that all study personnel received a uniform, centralised training was necessary to achieve an accurate understanding and mastery of the various criteria for cases (diagnosis, inclusion, exclusion, exclusion, shedding and termination criteria), the technical protocols of the treatment, the observational indicators and the scoring criteria. The case report form (CRF) was completed in its entirety and in accordance with the prescribed specifications, with no arbitrary alterations. Furthermore, observations of the same subject were recorded by the same individual whenever feasible.

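### The serious adverse event rule, as printed, terminates the trial after any such event, related or not; it should stop only the affected patient's study treatment

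*Protocol article*

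**What the plan says.** The rule is in the Adverse events section of the protocol article: "In case of any serious adverse event, whether related to the intervention, the trial should be terminated immediately". The sentence goes on "and appropriate rescue treatment initiated without delay". The phrase on relatedness is incomplete English, but its natural meaning is that the rule applies whether or not the event is related.

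The same section says of relatedness: "Adverse events during the treatment period were recorded and analysed to ascertain whether it was related to the treatment". It requires a report within 24 hours "to the responsible unit, the ethics committee, the sponsoring organisation" and to the drug regulator, and adds: "The relevant information must be recorded in the case file". The outcomes it lists for adverse events include hospitalisation and reduced capacity to work.

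Two other places bear on how the rule should be read. The Quality control section says that staff were trained on the "criteria for cases (diagnosis, inclusion, exclusion, exclusion, shedding and termination criteria", so termination is named there as something that applies to a case. The Study design section gives the assessment schedule: "Data were collected before treatment, after 4 weeks of treatment, and at 3 months and 6 months of follow-up".

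**The concern.** Two things look wrong.

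First, the rule acts on the trial rather than on a patient. A centre that followed it to the letter would treat one unrelated hospital admission as the end of a four-centre study. The section provides for a relatedness assessment and for a report to the bodies that could decide on continuation, but the rule uses neither before it acts.

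Second, limiting the rule to the affected patient does not fully repair it. Ending someone's part in a trial is wider than stopping the study treatment. The safety purpose is met by stopping treatment, giving rescue care and reporting. Ending participation as well puts later outcome assessments at risk without protecting the patient further. The sentence is not confined to the four treatment weeks, so it could also apply during follow-up, when no study treatment remains to be stopped.

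**Working it through.** The article gives no serious event rate and no stopping boundary, so there is no figure of the plan's own to reproduce. The check is a reading of the text plus some counting.

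**Step 1. What the sentence fixes.**
- Trigger: any serious adverse event.
- Relatedness: expressly set aside.
- Object: the trial.
- Timing: immediate.
- Number of events needed: one.
- Review before action: none.

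No other section of the article limits or overrides this.

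**Step 2. Signs that the patient was meant.**
- Termination is coupled with rescue treatment, which only a patient can receive.
- The record goes into the case file.
- The reporting sentence speaks of incidents in the plural, which fits poorly with a study that ends at the first one.
- Quality control places termination criteria among the criteria for cases.

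These favour a patient-level intent. None of them changes the words of the rule.

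**Step 3. Literal reading, illustration only.** Inputs: N = 166 (Sample size calculation) and an assumed per-patient risk p of a serious event over the study, which the article does not give. With independent patients all followed to the end, the chance of at least one event is 1 − (1 − p)^166.

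| Assumed p | Chance of at least one event |
|---|---|
| 0.1% | 15% |
| 0.5% | 56% |
| 1% | 81% |
| 2% | 97% |

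The table shows how sensitive a one-event rule is at this sample size. It applies only to the literal reading, and the conclusion does not rest on it.

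**Step 4. Patient-level reading.** The ODI is due at four times: baseline, week 4, month 3 and month 6. Three of these are after baseline. If participation and data collection both end at the event:

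| Event occurs | Post-baseline ODI values not collected |
|---|---|
| Before the week 4 assessment | 3 of 3 |
| Between week 4 and month 3 | 2 of 3 |
| Between month 3 and month 6 | 1 of 3 |

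For scale, the Sample size section says "the sample size of each group was the same", so 166 / 2 = 83 per arm. One patient is 1/83 = 1.2% of an arm. An arm has 83 × 3 = 249 post-baseline ODI values, and a patient lost before week 4 removes 3/249 = 1.2% of them. These counts describe what one such patient costs. They do not estimate how many there would be or how far the treatment difference would move.

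**The case against.** The strongest reply is that this is a slip of phrasing. The context points to the patient, and wording is loose elsewhere in the article. On that view, terminated may mean no more than that the study intervention stops, which is what the fix asks for. The sentence does not say that outcome assessments cease. The full termination criteria exist, since staff were trained on them, and they may settle the matter. Acting at once while also assessing relatedness is not a contradiction, because the assessment can serve safety reporting.

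Much of this stands. A patient-level intent is the likelier one. The loss of ODI values is inferred, not stated. The unseen criteria could resolve the question, and there is no contradiction between prompt action and a later relatedness assessment. What remains is that the article states a rule, and the rule as stated is too broad on its literal reading and wider than necessary on the kinder one. That is a fault in printed text, not a detail left to a fuller document.

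A reader might also infer that a terminated patient is removed from the analysis, because the Statistical analysis section drops subjects who were excluded from the trial. The documents do not support this. They nowhere link termination to exclusion, and Quality control lists the two as separate criteria.

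**Conclusion.** The point holds as a fault in the wording of a safety rule. Literally, one serious event of any cause is enough to stop the study. On the likelier reading, the rule ends one patient's participation when stopping study treatment would do. The cost is then up to three of three post-baseline ODI values for a patient who makes up 1.2% of an arm. That count assumes equal arms of 83 and that data collection ends with participation.

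The effect on the ODI result cannot be quantified. No event rate is given, and the direction of any effect is unknown. It is probably small. A reader might infer that the rule biases the primary comparison, or that the sponsor intended a one-event stopping rule for the whole study. The documents show neither: the first would need event numbers that they do not contain, and the context speaks against the second. Confidence is medium, because termination criteria that are not shown may already say what was meant.

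**What to change.** Reword the sentence in the Adverse events section to state that:

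1. A serious adverse event, related or not, stops the affected patient's study treatment and triggers rescue care and the existing 24-hour report.
2. Any decision to stop the whole trial is made by the sponsor and the ethics committee after that report, once relatedness has been assessed.
3. The outcome assessments already scheduled, up to six months, continue if the patient agrees.

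The cost is a short wording change and a notification to the ethics committee. Rescue care and reporting stay as they are. No visits or staff are added, because the follow-up schedule and the reporting route already exist.

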### Quality control

Prior to the implementation of the trial, ensuring that all study personnel received a uniform, centralised training was necessary to achieve an accurate understanding and mastery of the various criteria for cases (diagnosis, inclusion, exclusion, exclusion, shedding and termination criteria), the technical protocols of the treatment, the observational indicators and the scoring criteria. The case report form (CRF) was completed in its entirety and in accordance with the prescribed specifications, with no arbitrary alterations. Furthermore, observations of the same subject were recorded by the same individual whenever feasible.

### Data collection and management

A paper-based case record form was employed for data collection. The healthcare professionals proactively cooperated with the patients to complete the assessment of each outcome indicator and tolerantly answered the patients’ questions related to each assessment scale. Feedback was provided to patients promptly following each outcome assessment. The sub-centers used a uniform case record form for data collection. The case record forms were then reviewed by the subject leader and research assistant before submission to the data manager for data entry and management. The data were entered and managed by the data managers using an Excel database. To ensure the accuracy of the data, double-entry assessment and proofreading was conducted independently by the two data managers. In the event of uncertainty regarding the data entry on the case record form, the data administrator will complete the question-and-answer form and forward a query to the individual responsible for the subject matter through the research assistant. The individual responsible for the subject matter should provide a response as soon as possible. The data administrator will then modify, confirm and enter the data in accordance with the response provided by the individual in charge of the subject matter. Once the database has been confirmed to be error-free, it will be locked by the subject person in charge, the data manager and the statistical analyst. The data collected from subjects will not be made public without their consent.

### Statistical analysis

The data will be subjected to analysis by our team of professional statisticians, who will employ IBM SPSS Statistics V.27.0 for this purpose. To assess the normality of the data, the Kolmogorov–Smirnov test was used. The quantitative results were expressed in terms of the mean and standard deviation. The purpose of the primary and secondary outcome indicators was to assess the difference in efficacy between the two groups. Hypothesis testing was employed to this end. The chi-square test was used to ascertain the dissimilarities in baseline data between the two groups. The analysis of variance for repeated measures was utilised to examine the alterations in efficacy between the two groups before, during and after the intervention, as well as after the follow-up period. For confounding factors that were challenging to regulate or were not regulated prior to treatment, such as an imbalance between the groups prior to treatment, were treated as covariates, and logistic regression was employed to ascertain the variability of efficacy between groups and to eliminate the influence of these factors on efficacy. The data collection and data summarisation were meticulously examined to minimise data anomalies. In the event of missing data, the data were assumed to be missing at random, and multiple interpolation would be employed for analysis. Subjects who were excluded from the trial will be excluded from the data set. The level of statistical significance was set at 5% (*p* < 0.05), and 95% confidence intervals were employed as effect estimates.

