### Primary outcome

The ODI scale, which consists of 10 items in 3 dimensions, namely pain, individual functioning and overall personal functioning, was used as a comparison of efficacy before and after treatment and between groups (28). The maximum score was 50; the higher the score, the higher the degree of dysfunction of the patients.

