### Secondary outcome

The SF-36 Scale evaluates health in eight dimensions, including physical functioning, general mental health and social functioning, and higher scores indicate better health (29). Each dimension was rated with a maximum of 100 points and a minimum of 0 points.

The SF-MPQ Scale includes three parts: pain rating index (PRI), (VAS) and present pain intensity (PPI) (30). The PRI assesses the patient’s emotional and sensual experiences of pain. The VAS provides a straightforward visual representation of the patient’s pain level. The PPI determines the intensity of the patient’s current pain on a six-point scale (0–5).

Gait analysis is the process of collecting patient information using a wearable 3D gait analyser. Gait analysis encompasses a range of patient data, including step length, cadence, stride length and double support phase. This information is utilised to assess the patient’s motor function and musculoskeletal rehabilitation status (31).

After all the relevant items were confirmed by the patients themselves, the total score reflecting the degree of low back and leg pain in each period was calculated cumulatively by a specialised statistician, and the results were used for pre- and post-treatment comparisons as well as comparisons between groups.

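### The plan names a chi-square test for baseline data that are mostly numeric and ties adjustment to observed imbalance, so a chance imbalance in a numeric variable may be left unadjusted

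*Protocol article*

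**What the plan says.** All the analysis statements come from the Statistical analysis section of the protocol article.

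- Baseline comparison: "The chi-square test was used to ascertain the dissimilarities in baseline data between the two groups". The sentence is not limited to categorical variables, and no other baseline comparison is named.
- Adjustment: factors that were hard to control, or were not controlled before treatment, "such as an imbalance between the groups prior to treatment, were treated as covariates". The model named is logistic regression: "logistic regression was employed to ascertain the variability of efficacy between groups and to eliminate the influence of these factors on efficacy".
- Main comparison over time: "The analysis of variance for repeated measures was utilised to examine the alterations in efficacy between the two groups before" and at the later visits.
- Summaries: "The quantitative results were expressed in terms of the mean and standard deviation".

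Other sections show what the baseline data are. Under Primary outcome, the ODI is a numeric score: "The maximum score was 50". Under Secondary outcome, the SF-36 is numeric: "Each dimension was rated with a maximum of 100 points and a minimum of 0 points". That section also lists the VAS and gait measures such as step length and cadence. The inclusion criteria add age (18 to 65 years), disease duration (at least 3 months) and VAS (above 3, up to 7).

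**The concern.** A chi-square test compares counts across categories and ignores order and distance. To use it on an ODI or SF-36 score, the analyst must treat every distinct value as a category or cut the score into bands. Both discard information about a difference in means, and the article gives no banding. It does recognise these variables as numeric, since it summarises quantitative results by mean and SD.

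This matters because adjustment is described as a response to factors such as an observed imbalance. The section does not say how imbalance is recognised, and the only tool it offers is unsuitable for the variables most related to outcome, above all baseline ODI. No covariate is fixed in advance. A chance difference in baseline ODI could therefore stay in the between-group comparison. The choice of covariates could also depend on what is seen in the data.

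**Working it through.** **Inputs.** Total sample 166, allocated 1:1, so 83 per group (Sample size calculation). SD 2.60, a 4-week figure from the earlier study (same section). Two-sided 5% level. The baseline ODI SD and the correlation r between baseline and follow-up are not given. I assume equal SDs at both visits and r from 0.3 to 0.7.

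**The plan's own figure.** The 74 per group reproduces with the denominator squared: 2 × (1.96 + 0.8416)² × 2.60² / (5.2 - 4)² = 73.69, rounded up to 74. The present point does not depend on it.

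**1. Chance imbalance to expect.** Under sound randomisation the true baseline difference is zero. The observed standardised difference b has standard error √(2/83) = 0.155. Its two-sided 5% limit is 1.96 × 0.155 = 0.30 SD. A difference of 0.5 SD or more corresponds to z = 0.5/0.155 = 3.22, with probability about 0.0013 per variable (roughly 1 trial in 780).

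**2. What an imbalance does to each contrast.** Given b, with equal SDs and no other difference between groups:

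- post-treatment difference: error = r × b
- change from baseline (the group-by-time contrast): error = r × b - b = -(1 - r) × b
- baseline entered as a covariate in a linear model: error about 0

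| b (SD) | r | Post-treatment error (SD) | Change error (SD) |
|---|---|---|---|
| 0.155 | 0.3 | 0.05 | -0.11 |
| 0.155 | 0.7 | 0.11 | -0.05 |
| 0.30 | 0.3 | 0.09 | -0.21 |
| 0.30 | 0.5 | 0.15 | -0.15 |
| 0.30 | 0.7 | 0.21 | -0.09 |

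For scale, the unadjusted post-treatment difference itself has a standard error of 0.155 SD.

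**3. Precision.** Relative to the post-treatment contrast (variance 1), the change contrast has variance 2(1 - r) and the covariate-adjusted contrast 1 - r².

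- r = 0.3: 1.40 and 0.91
- r = 0.5: 1.00 and 0.75
- r = 0.7: 0.60 and 0.51

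Adjustment is the most precise of the three across this range.

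**4. Does chi-square see the same imbalances as a test on means?** This was simulated at 83 per group with no true difference, the relevant case under randomisation (10,000 trials). A t-test flags 4.8% of trials and a median-split chi-square 6.2%. The chi-square misses about 50% of the trials that the t-test flags. If a true difference of 0.3 to 0.5 SD is imposed, the t-test detects 48% to 89% and the median-split chi-square 37% to 76%. The loss depends on the categorisation, which the article does not state.

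**The case against.** The strongest reply has four parts.

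**No stated gate.** No sentence makes the chi-square p-value decide adjustment, and imbalance is given as one example of a factor to adjust for. This stands. A reader might infer that real imbalances are left uncorrected, but the article does provide for adjustment. What can be said is that the route from baseline comparison to covariate is undefined, and that the only comparison named does not suit numeric data.

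**Baseline is already in the ANOVA.** This stands as a fact but does not settle the matter. Including the pre-treatment visit as a repeated measure gives a change contrast with error -(1 - r) × b. It does not remove the imbalance.

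**Large miss rates and shifts are not supported.** A reader might infer that chi-square would miss most imbalances: about 85% at a 0.5-SD difference if every raw ODI score is its own category and the SD is 6. A reader might also infer that the result would move by 0.4 to 0.9 ODI points. Both figures presuppose a 0.5-SD imbalance, which is rare under randomisation. The first also needs a raw-score table that the plan does not mention. Neither should be used as the size of this problem.

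**Condensation.** The full plan may use chi-square for categorical variables only. That is possible and lowers the severity. The sentence as printed is nevertheless unrestricted, so it is a statement to correct and not a missing detail.

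**Conclusion.** The point holds in a limited form. The article assigns a test for categorical data to baseline data that are mostly numeric, and it leaves baseline adjustment to depend on an imbalance whose recognition is not defined. A chance imbalance in a numeric variable may therefore go unadjusted.

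At the 5% limit of chance imbalance (0.30 SD) the error is 0.09 to 0.21 SD, in opposite directions for the post-treatment and change contrasts. This rests on 83 per group, equal SDs and an assumed r of 0.3 to 0.7. Most trials would have a smaller imbalance. Randomisation keeps the unadjusted comparison unbiased on average, so the loss is one of precision and of protection against chance imbalance, not of validity. Severity is minor to moderate.

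Replacing chi-square with a t-test would not cure it, because no baseline significance test is a sound basis for choosing covariates.

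**What to change.** In the Statistical analysis section:

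- Limit the chi-square test to categorical baseline variables such as sex.
- Describe numeric baseline variables by mean and SD, or median and IQR if skewed, and state that no baseline test decides adjustment.
- Enter the baseline value of each numeric outcome as a covariate in its between-group analysis (linear model, ANCOVA or mixed model), whatever balance is observed. For these numeric outcomes, this takes the place of the logistic regression now named for adjustment.

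The cost is a few sentences. The baseline values are already collected, and no extra patients or visits are needed. The assumed range of r suggests a gain in precision at no cost.

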### Outcomes

The efficacy evaluation in this study concentrated on the primary outcome indicator, namely the recovery of dysfunction in patients before, after and during the follow-up period. In addition, several secondary indicators were evaluated, including quality of life, pain and gait analysis. The data collection at each time point was conducted by independent researchers who were not privy to the specific subgroups and were not involved in other aspects of the study. The specific time points for data collection are presented in Figure 4.

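### The trial is sized on the 4-week ODI difference beyond a margin of -4, but the repeated-measures ANOVA named for the comparison has no term that tests that hypothesis

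*Protocol article*

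**What the plan says.** **Sample size calculation.** The section states: "The trial was designed as a superiority trial with ODI as the primary observation index". Its inputs are 4-week values: "the mean and standard deviation of ODI after 4 weeks of intervention in the TCEs group were 19.73 and 1.94, respectively", and "mean and standard deviation of ODI after 4 weeks of intervention in the Tuina combined with TCE group were 14.53 and 2.60, respectively" for the combined arm. With alpha 0.05 (two-sided quantile), beta 0.2, sigma 2.60 and a margin of -4, it arrives at 74 per group. The planned total is 166.

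**Outcomes and Primary outcome.** The primary indicator is described as "namely the recovery of dysfunction in patients before, after and during the follow-up period". The ODI "was used as a comparison of efficacy before and after treatment and between groups". Neither section singles out a visit, and the second puts before-after change beside the between-group comparison.

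**Statistical analysis.** "The analysis of variance for repeated measures was utilised to examine the alterations in efficacy between the two groups". The sentence goes on to list times before, during and after the intervention and after follow-up, so baseline is a level of the outcome. Study design gives four assessments: baseline, 4 weeks, 3 months and 6 months. It lists none during treatment. The section does not say which ANOVA term decides the trial and does not mention the -4 margin. The only covariate-adjusted method it names is logistic regression, which does not estimate a mean ODI difference.

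**The concern.** A sample size supports a claim only if the analysis tests the hypothesis that was sized. Here the sizing refers to one visit, one direction and a non-zero null. The ANOVA refers to four visits and, by default, a null of zero. A repeated-measures ANOVA offers a group main effect, a group-by-time interaction and any contrast taken from the model, and these answer different questions. Without a stated choice, readers cannot tell which result counts as success or whether success means any difference or a difference beyond 4 points. If the choice is made after the data are seen, the 80% power statement attaches to nothing in particular.

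**Working it through.** **Inputs from the protocol article.** 4-week means 14.53 (combined) and 19.73 (TCE); sigma 2.60; margin -4; two-sided alpha 0.05; power 0.80; 1:1 allocation; 74 per group; four visits.

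**Assumptions not in the document.** Equal baseline means through randomisation; SD 2.60 at every visit in both arms; compound symmetry with correlation rho from 0.3 to 0.7; normal approximation, except for the interaction F test.

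**1. Reproducing the stated size.** The planned difference is 14.53 - 19.73 = -5.20. The distance beyond the margin is -5.20 - (-4) = -1.20.

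n = 2 x (1.96 + 0.84)^2 x 2.60^2 / 1.20^2 = 73.7, rounded up to 74.

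The stated figure is reproduced, provided the denominator is squared; as printed, without the square, the formula gives -88.4. Against a null of zero the same inputs would need 2 x (1.96 + 0.84)^2 x 2.60^2 / 5.20^2 = 3.9, about 4 per group. So 74 belongs to the margin hypothesis at 4 weeks.

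**2. A 4-week contrast against -4.** The standard error is 2.60 x sqrt(2/74) = 0.427, and 1.20 / 0.427 = 2.81. Power is Phi(2.81 - 1.96) = 80.2%. With 83 per group (166/2) it is 84.5%. Adjusting for baseline ODI at rho = 0.5 gives 2.81 / sqrt(1 - 0.25) = 3.24 and power of about 90%.

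**3. The ANOVA group main effect.** This compares the mean of four visits, one of which has an expected difference of zero. In absolute points:

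| Course of the effect | Four-visit average |
|---|---|
| Sustained (0, 5.20, 5.20, 5.20) | 3.90 |
| Halved at follow-up (0, 5.20, 2.60, 2.60) | 2.60 |
| 4 weeks only (0, 5.20, 0, 0) | 1.30 |

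All three fall short of 4. The SE of the averaged difference is 2.60 x sqrt((1 + 3 rho)/4) x sqrt(2/74), which is 0.338 at rho = 0.5. In the sustained case the chance of showing superiority beyond the margin is Phi((3.90 - 4)/0.338 - 1.96) = 1.2%. It is 1.1% at rho = 0.3 and 1.3% at rho = 0.7. In the other two cases it is essentially zero.

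**4. The same main effect against zero.** The worst case is an effect at 4 weeks only. At rho = 0.5, Phi(1.30/0.338 - 1.96) = 97.0%. Over rho 0.3 to 0.7 it runs from 99.3% down to 93.3%. The sustained and halved courses give practically 100%.

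**5. The group-by-time interaction.** With four visits it has 3 degrees of freedom. Its noncentrality is (74/2) x SS / (2.60^2 x (1 - rho)), where SS is the sum of squared deviations of the visit effects from their mean. In the sustained case SS = 3.90^2 + 3 x 1.30^2 = 20.28, so at rho = 0.5 the noncentrality is 222. Power against zero is about 100% for all three courses and all three values of rho. A significant result would say only that the arms' profiles over time differ. It would not say in which direction, at which visit or by how much.

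**The case against.** The strongest reply is that the plan is loose rather than wrong. The ANOVA is never labelled primary. The wording about changes in efficacy reads naturally as the group-by-time interaction, for which baseline is a reference and not a dilution. A 4-week contrast with its confidence interval can be taken from the same model, 95% intervals are promised, and the choice of contrast is often left to a statistical analysis plan.

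Part of this stands. A 4-week contrast is available from the model, and a separate plan could specify it. But the article itself fixes both a sample-size hypothesis and a between-group method, and the two do not meet. The ANOVA is the only between-group test it names for repeated continuous scores. Reading it as the interaction supplies neither a visit nor the margin.

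Three stronger readings are tempting, and the document does not support them:

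- **That the trial would miss a real 4-week effect through dilution.** Group-effect power of 76% (sustained) or 14% (gone by 3 months) at rho = 0.5 results from taking 1.20/2.60 = 0.46 SD as the effect and testing it against zero. That 0.46 SD is the excess over the margin. The planned effect is 5.20/2.60 = 2.0 SD.
- **That the false-positive rate is about 12%.** This needs a rule under which any one of three visits tested at 5% counts as success. No such rule is stated.
- **That patients with a missed visit are dropped.** The Statistical analysis section assumes data missing at random and plans what is evidently multiple imputation.

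**Conclusion.** The point holds as a mismatch of hypothesis, estimand and decision rule. The stated 74 per group fits one test, the 4-week ODI difference against -4, and the article does not name that test. On the planned effect, the group main effect targets at most 3.90 points and has about a 1% chance of showing superiority beyond the margin. The interaction does not address the margin at all. These figures rest on the assumptions of equal SDs and compound symmetry. The 3.90 itself needs only equal baseline means, a fully sustained effect and four equally weighted visits. A reader might infer that the trial is underpowered. Against zero it is not: power is at least about 93% at the planned effect. What is unsettled is which result decides, and against which null.

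**What to change.** Name the between-group difference in ODI at 4 weeks as the single primary comparison. Estimate it with a 95% confidence interval by ANCOVA, or by a mixed model on the post-baseline visits with arm-by-visit terms, with baseline ODI as covariate in either case. Test it against the -4 margin used for sizing: superiority is shown if the whole interval for combined minus TCE lies below -4. If the intended null is zero, say so and restate the sample-size basis, because 74 per group does not come from that null. Report the 3- and 6-month contrasts as secondary, and do not use within-group before-after changes as evidence of efficacy.

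The cost is a change of wording and no new sample size: power against -4 at 74 per group is about 80% unadjusted, and about 90% with baseline adjustment if the baseline to 4-week correlation is 0.5 (an assumption). The change should be made before the data are analysed, so that the deciding test is not chosen in sight of the results. The downside is that a benefit seen only at 3 or 6 months would not count as primary.
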